#### Neuropsychological assessment

Data are acquired using a 3-tesla Siemens Verio magnetic resonance imaging (MRI) scanner (Erlangen, Germany) with a standard Siemens 32-channel phased array head coil. The MRI protocol includes acquisition of (1) resting-state functional MRI (7 min), (2) T1-weighted imaging (4 min), (3) fluid attenuated IR (FLAIR) (4 min), (4) diffusion weighted imaging (DWI) (8 min), for a total of under 23 min of scanning. Resting-state fMRI will be conducted to measure functional region connectivity, and DWI to measure anatomical region connectivity. T1-weighted images and FRAIR images will be used for the volumetric analysis. Participants who meet any exclusion criteria for MRI (e.g., currently pregnant; currently breastfeeding; wearing pacemaker, aneurysm clips, or other implants) will be excluded from the MRI scan.

### Procedure for assessment; blinding

Independent evaluators not involved with the intervention for or coordination of this clinical trial will conduct the SCID-IV-TR, GRID-HAMD, SIGH-A, and rate CGI and GAF. These independent evaluators are prohibited from accessing any information that could confer participant assignment. Independent evaluators need to be trained at least 20 h to be eligible to serve. For the primary outcome of GRID-HAMD, the evaluators trained by attending workshops, watching a training DVD, role-play with a mock patient, direct observation of evaluation, and conducting GRID-HAMD with patients. All evaluator assessments will be recorded and used for other evaluator ratings to examine the reliability of the assessment. We will choose one-fifth of the assessments using the same random sampling technique as for treatment adherence, and examine assessment integrity on their basis.

The independent evaluators will respond to the modified version of the Independent Evaluator Knowledge of Treatment scale at mid (10 weeks), post (21 weeks) and follow-up assessment (43 weeks). This three-item scale for assessing the evaluator’s knowledge of patient assignment has been used in clinical trials of cognitive behavior therapy for panic disorder as well as the unified protocol for emotional disorders [112]. The independent evaluators give their conjectures, rate their confidence in their answer, and provide any relevant information that led to the conjecture.

### Data management and monitoring

Acquired data will be entered immediately into a database constructed using Microsoft Access. Each entry form will be restricted to the possible range of items. Data entry and verification will be conducted independently by study assistants. Central and onsite monitoring will be conducted periodically by a data manager at NCNP throughout the course of the trial.

### Sample size calculation

Because this clinical trial is intended to examine the efficacy of a novel treatment (the unified protocol) that targets clinical populations that are heterogeneous in terms of a traditional diagnostic perspective, we had to collect information on the treatment effect size from various sources in order to estimate the sample size. Estimation was based on information from previous findings on efficacy of transdiagnostic and disorder-specific CBT for depressive and anxiety disorders, results of our pilot study, and previous randomized controlled trials of the unified protocol among U.S. participants [38, 68].

Meta-analysis of the RCT to examine the effect of CBT in comparison to waiting-list on major depressive disorder reported a standardized mean difference (SMD) of 0.82–0.85 [113, 114]. For anxiety disorders by DSM-IV criteria, separate meta-analysis of RCT comparing CBT with waiting-list or seemingly equivalent condition (e.g., no treatment, or placebo attention control) showed an effect size of 0.82 for generalized anxiety disorder (*n* = 4) [115], 0.91 for panic disorder with/without agoraphobia (*n* = 7) [116], 0.93 for social anxiety disorder (*n* = 7) [117], and 1.36–1.70 for posttraumatic stress disorder (*n* = 21) [118]. Finally, other meta-analysis reported a large effect size of CBT against waiting-list or active placebo control for emotional disorders (SMD = 0.63–1.09) [119, 120].

There are few previous findings on the efficacy of the unified protocol. In the pilot randomized controlled trial comparing with waiting-list, an SMD of 0.52–1.11 for depression measures and 1.10 for anxiety measures was observed among patients with anxiety disorders [38]. Our pilot clinical trial of the unified protocol among Japanese patients with depressive and anxiety disorders demonstrated a within SMD of 1.70 (95 % CI = 0.81–2.67) for GRID-HAMD, 1.14 (95 % CI = 0.40–1.89) for ODSIS, 0.76 (95 % CI = −0.05–1.57) for BDI-II, 1.29 (95 % CI = 0.56–2.06) for SIGH-A, and 1.71 (95 % CI = 0.91–2.50) for OASIS [68].

Summarizing these findings, we assumed a large effect size of 0.85 for UP with TAU against waiting-list with TAU for the reduction of primary outcome assessed by GRID-HAMD. Using G*Power, in order to detect the difference between groups with a statistical power of 80 % for a two-tailed test, the needed sample size was calculated to be 23 for each group. In consideration of reported dropout rates of 11.76–15.39 % in previous studies [38, 68], we assumed a dropout rate of 15 % and a need to have at least 27 participants in each group to test the primary hypothesis of this study (difference of GRID-HAMD scores between intervention and control groups over the 21-week period). We will continue recruiting patients for ancillary study of neuroimaging, treatment process, and mechanism.

Two separate meta-analyses reported the effect size of transdiagnostic cognitive-behavioral treatment *after* we had finished designing this clinical trial and had started the actual trial [32, 33]. These latest analyses showed the effects of transdiagnostic treatments (including individual, group, and internet format) with control group (waiting-list, supportive counseling, psychoeducation, TAU, online support, or discussion forum) on the self-report measure of anxiety (SMD = .65, 95 % CI = .34–.57, *n* = 24) and depression (SMD = .80, 95 % CI = .62–.98, *n* = 22). Reinholt and Krogh [33] reported pooled SMD for four RCTs testing the efficacy of transdiagnostic individual or group treatment in comparison to waiting-list controls as −1.00 (95 % CI −1.74–-0.26). Taking into account this information, our estimation might have been a bit optimistic, suggesting the risk that our method is underpowered to test our primary hypothesis.

### Statistical methods

All analyses for testing efficacy of treatment on primary and secondary measures will be analyzed on the basis of the intent-to-treat principle, using a linear mixed model (LMM). The LMM approach was selected because of its strength in dealing with missing data and its ability to incorporate random effects (i.e., of the participants) into the analyses. For the primary outcome, the dependent variable is the GRID-HAMD score, and the independent variables are assignment (i.e., intervention vs. control group), time (i.e., 0, 10, and 21 weeks), and interaction of the assignment and time, as a fixed-effect variable, and participants, as random-effects variable. We will construct a conditional growth model [121] using a restricted maximum likelihood estimation method to compare changes in depression severity between groups from baseline to 21 weeks. The assessment period is measurement time for the growth model (weeks 0, 10, and 21), which will be coded as an ordinal scale (0, 1, 2). We assume an unstructured error covariance for this model. If the analysis will not converge, we will use other covariance structures. The covariance structure that will show convergence of the analysis and best fit to the data, evaluated by Akaike’s information criterion, will be used as the primary analysis.

To test robustness, we will conduct the same LMM, including a stratified variable (depressive vs. anxiety disorder) as covariate and other sensitive analyses taking into account the following aspects: ITT vs. per-protocol, and multiple imputation methods for missing data [122]. Secondary outcomes will be analyzed in the same way as primary outcomes. For all analyses, *P* < .05 will be considered statistically significant. The other statistical analyses will be conducted to examine treatment mechanism, process, and neurological implications in relation to outcome.

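### The primary mixed model leaves the week-0 GRID-HAMD mean free in each arm and so gives away precision that a shared baseline mean or baseline adjustment would recover. The SD behind the effect size of 0.85 is not stated.

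*Protocol article*

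**What the plan says.** Under Statistical methods, the response is the GRID-HAMD score. The fixed effects are assignment, "time (i.e., 0, 10, and 21 weeks), and interaction of the assignment and time, as a fixed-effect variable", with a random effect for participants. Time is coded 0, 1, 2 and the error covariance is unstructured. The model is meant "to compare changes in depression severity between groups from baseline to 21 weeks". Neither a common baseline mean nor a baseline covariate is specified. The only covariate named, for a robustness check, is the depressive-versus-anxiety stratification factor.

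Under Sample size calculation, "we assumed a large effect size of 0.85 for UP with TAU against waiting-list with TAU for the reduction of primary outcome assessed by GRID-HAMD". Then, "with a statistical power of 80 % for a two-tailed test", "the needed sample size was calculated to be 23 for each group". This becomes 27 per group for 15% dropout. The evidence summarised there includes a meta-analysis of CBT against waiting-list in major depressive disorder that "reported a standardized mean difference (SMD) of 0.82–0.85". No GRID-HAMD SD and no baseline-to-week-21 correlation is given, and the SD by which 0.85 is standardised is not stated.

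The endpoint is described in two ways: as depression at 21 weeks in the Abstract, and as change over the intervention period under Primary outcome.

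**The concern.** With time coded 0, 1, 2, the assignment main effect is the week-0 difference between arms. Allocation is randomised 1:1, so that difference is zero in expectation. The model estimates it all the same, and the assignment-by-time term is measured from it. The result is a difference in change, which subtracts baseline in full whatever its correlation with the outcome.

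The stake is precision in a trial of 27 per arm. The sample size section itself concedes that the study may be underpowered, on account of the effect size. The baseline scores are collected anyway, so the information is available without cost.

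A second, smaller matter is that 0.85 could be in units of the SD of the score or of the SD of change. The reader therefore cannot match the stated power to the stated test.

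**Working it through.** **Inputs from the protocol.** d = 0.85; 23 per group before dropout; 80% power, two-tailed (Sample size calculation). Significance level: "For all analyses, *P* < .05 will be considered statistically significant" (Statistical methods).

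**Assumed, because the protocol does not give them.** The SDs s0 (week 0) and s21 (week 21), and their correlation ρ. Ranges are shown.

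**1. The plan's own figure.** Two-sample t-test with noncentral t: noncentrality 0.85 × √(23/2) = 2.88 on 44 df gives 80.5% power; 22 per group gives 78.6%. The 23 reproduces. Also 27 × 0.85 = 22.95, so 27 is consistent with 15% dropout.

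**2. Variance per patient of the endpoint contrast.**
- Change: s0² + s21² − 2ρ·s0·s21
- Baseline-adjusted: s21²(1 − ρ²)
- Difference: (s0 − ρ·s21)², which is never negative and vanishes when ρ = s0/s21

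With equal SDs these become 2(1 − ρ) and 1 − ρ² in units of the squared SD. Their ratio is (1 − ρ²)/[2(1 − ρ)] = (1 + ρ)/2, that is 0.65 at ρ = 0.3, 0.75 at 0.5 and 0.85 at 0.7.

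**3. Power if 0.85 is in score-SD units (equal SDs, 23 per arm, no missing data).** The effective d is 0.85/√(2(1 − ρ)) for change and 0.85/√(1 − ρ²) adjusted (43 df).

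| ρ | d, change | Power, change | d, adjusted | Power, adjusted |
|---|---|---|---|---|
| 0.3 | 0.718 | 66% | 0.891 | 84% |
| 0.4 | 0.776 | 73% | 0.927 | 87% |
| 0.5 | 0.850 | 80.5% | 0.981 | 90% |
| 0.6 | 0.950 | 88% | 1.062 | 94% |

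The planned test reaches the stated power at ρ = 0.5 and exceeds it above that.

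**4. The planned slope, with week 10 used.** The 0/1/2 slope was checked by generalised least squares with known covariance, equal SDs and 23 per arm. Under compound symmetry or an autoregressive pattern, week 10 adds nothing and the free-baseline figures in step 3 stand. Other patterns differ. Correlations are listed in the order weeks 0–10, 10–21, 0–21.
- 0.4/0.7/0.4: raw change 73%, planned slope 79%, same slope with a shared week-0 mean 88%
- 0.3/0.7/0.2: raw change 61%, planned slope 69%, shared mean 84%

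**5. SDs that grow over time (0.85 in units of the week-21 SD).** Endpoint contrast, change against adjusted:
- SD 4 to 6: 79% vs 84% at ρ = 0.3; 84% vs 87% at 0.4; 89% vs 90% at 0.5
- SD 4 to 7: 81% vs 84% at ρ = 0.3; 90% vs 90% at 0.5

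For the 0/1/2 slope, free against shared week-0 mean, the gap ran from about 7 points (SDs 4, 5, 6 with correlations 0.3/0.7/0.2: 76% vs 82%, unrounded gap 6.7) to almost nothing (SDs 4, 6, 7 with 0.6/0.7/0.5: both about 90%). The shared mean had the lower variance in every SD and correlation pattern tried.

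**6. Power if 0.85 is in units of the SD of change.** The planned test has 80.5% at any ρ. Adjusted d is 0.85 × √[2/(1 + ρ)] at equal SDs, giving 94%, 90% and 86% at ρ = 0.3, 0.5 and 0.7.

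**The case against.** The strongest objection concerns power. A reader might infer that sizing and analysis disagree, so that the trial lacks its stated 80% unless ρ is at least 0.5. The protocol does not support that. The sample size sentence attaches 0.85 to the reduction in the primary outcome, Primary outcome defines that outcome as change, and the model tests change. On that reading sizing and test agree at every correlation. A between-group SMD can be standardised by either SD, and nothing in the protocol settles which was used. Nor does it support calling a low correlation likely. This objection stands in full.

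Three further objections stand in part:
- The widest gap (66% against 84%) depends on equal SDs, score-SD units and an endpoint contrast that ignores week 10. Entry requires GRID-HAMD of at least 8, which truncates baseline, so a smaller SD at week 0 than at week 21 is plausible. That shrinks the gain, although a mild ratio of 0.8 at ρ = 0.3 still leaves 74.5% against 84.0%.
- Adjustment does not guarantee 80% at every correlation. At ρ of 0 to 0.1 in score-SD units, adjusted power is about 79.5–80% once the estimated coefficient is counted.
- The planned model is valid, and change already accounts for baseline in part. This is true, and it makes the point one of efficiency. It does not remove the case for an improvement that needs no new data.

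**Conclusion.** The point holds as a loss of precision, not as bias and not as a demonstrated power shortfall. With equal SDs the planned contrast carries 1/0.65 = 1.54 times the variance of the adjusted one at ρ = 0.3, and 1/0.85 = 1.18 times at ρ = 0.7. In power terms the loss runs from 18 points (ρ = 0.3, score-SD units, equal SDs, week 10 uninformative) to almost nothing (ρ close to s0/s21). All these figures rest on assumed SDs and correlations, and the slope figures also on a treatment effect linear in the coded time, as the planned model already has it.

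The standardiser is a separate reporting gap. Until the protocol says which SD 0.85 refers to, the 80% can be neither confirmed nor refuted for the planned test.

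**What to change.** 1. In the same model and with the same 0, 1, 2 coding, drop the assignment main effect and keep time and assignment-by-time, so that both arms share one week-0 mean. Every randomised patient stays in, including those with a baseline score only.
2. Alternatively, make weeks 10 and 21 the responses and adjust for baseline GRID-HAMD. Patients without a later score then contribute nothing, so the shared mean is the better choice.
3. State which SD 0.85 refers to and the assumed baseline-to-week-21 correlation, and restate the power for the chosen analysis, over a range of correlations if none is known.
4. Use one description of the endpoint, week-21 level or change, in the Abstract and under Primary outcome.

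Moving to categorical time with a test at week 21 is a separate choice. It changes the tested contrast, can be marginally less efficient than the planned slope, and is not needed here.

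The cost is one term in the model and a few lines of text, with no new data and no patients lost. With 44 of 54 participants enrolled at submission, the change should be fixed before anyone sees outcomes by arm.

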## Methods/design

### Trial design, randomization, and ethical aspects

This study is a single-center, assessor-blinded, randomized, parallel-group superiority design with a target sample of 54 patients with depressive or anxiety disorders. Participant flow is depicted in Fig. 1. We will employ central randomization using Allocation and Registration Control System (ARCS) computer software, set up and managed independently of the study by the Project Management Office at the Keio Center for Clinical Research. A random sequence will be generated using minimization, with a ratio of 1:1 to balance stratified factors (depressive vs. anxiety disorder). Allocation will be implemented by the primary investigator or research coordinator via internet using a laptop in front of the eligible participant. This protocol has been reviewed and approved by the institutional review board of the (Japanese) National Center of Neurology and Psychiatry (accepted on October 18, 2013; A2013-092). All participants will give written informed consent to participation in the study. This trial is registered within ClinicalTrials.gov, number NCT02003261.

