## Discussion

Completion of this clinical trial will add to the evidence of efficacy for transdiagnostic psychological treatment of emotional disorders, which is not conclusive at this time [32, 33]. This trial has importance especially with regard to the question of the efficacy of UP for depressive disorders and in an Asian population. UP is considered to be promising as a treatment for depressive disorders because of the enormous efficacy shown in existing findings for treatment of this disorder by diagnosis-specific CBT [18, 113, 123]. There seems to be no reason to expect weaker efficacy with UP, and there is some reason to expect enhanced efficacy of UP on depressive disorders. That is, one of the core modules of UP is emotion exposure, and the rationale of “avoiding avoidance” was originally considered important for treatment of anxiety disorders; however, recent advances in the understanding of behavioral activation lead us to regard avoidance as a key maintenance factor for depression. Further, positive as well as negative emotion regulation has been found to be an important treatment target [124]. The UP has been modified to incorporate these findings in order to enhance its efficacy [37].

Transdiagnostic treatments have several strengths, including versatility to treat a broad range of emotional disorders, and the relative parsimony of learning core principles of cognitive behavioral therapy. These strengths are especially important to clinical practice in Japan, which has many barriers that hinder patients from receiving evidence-based treatments and where there are severe problems for the dissemination of CBT [125]. Only three randomized controlled clinical trials have been conducted to assess the efficacy of CBT in medical settings in Japan (one trial each for obsessive–compulsive disorder, insomnia, and hypochondria). If its efficacy is confirmed by the present study, this versatile treatment will contribute to the more rapid adoption of evidence-based treatment to those who need it for emotional difficulties in Japan.

In addition to the results for the primary hypothesis, secondary analyses of treatment mechanism, process, and neurological correlates will inform better implementation of the unified protocol, and, possibly, other transdiagnostic treatment.

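### Diagnosis, the one minimisation factor, is left out of the primary model, and the robustness model that adds it, read plainly as a main effect, cannot test whether the result depends on it

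*Protocol article*

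**What the plan says.** Under Trial design, randomization, and ethical aspects, the protocol article states the allocation method: "A random sequence will be generated using minimization, with a ratio of 1:1 to balance stratified factors (depressive vs. anxiety disorder"). No other balancing factor is named.

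Under Statistical methods, the primary model for GRID-HAMD has these fixed effects: "assignment (i.e., intervention vs. control group), time (i.e., 0, 10, and 21 weeks), and interaction of the assignment and time, as a fixed-effect variable", with participant as random effect. Its purpose is to "compare changes in depression severity between groups from baseline to 21 weeks". Time is a variable "which will be coded as an ordinal scale (0, 1, 2"), and on covariance the text says: "We assume an unstructured error covariance for this model". The diagnostic factor is not in this list.

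The factor enters once, as a check: "To test robustness, we will conduct the same LMM, including a stratified variable (depressive vs. anxiety disorder) as covariate". No interaction of the factor with time is stated. Secondary outcomes are to be analysed in the same way.

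**The concern.** Two things follow from the text.

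First, the robustness check does not probe what it appears to probe. The primary comparison is between changes from baseline, and week 0 is itself a response in the model. A main effect of diagnosis raises or lowers all three visits of a patient by the same amount, so it drops out of any change. The result will look robust to diagnosis almost by construction, and could be reported as if it had been tested. The same holds for continuous secondary outcomes such as SIGH-A.

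Second, minimisation removes most of the between-arm variation that diagnosis could cause, while a model without diagnosis still counts that variation as error. If diagnosis is related to change in GRID-HAMD, the standard error is then too large and power is lost. The target is 54 patients, and the sample size section itself concedes that the trial may be underpowered.

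**Working it through.** **The plan's own figure.** Inputs from Sample size calculation: SMD 0.85, power 80%, two-tailed, 15% dropout. Alpha 0.05 comes from Statistical methods. For a two-sample t-test with noncentrality 0.85 × √(n/2), power is 0.786 at n = 22 and 0.805 at n = 23 per group, so 23 reproduces. Dropout: 23/0.85 = 27.06, stated as 27. With all 27 per group evaluable, power is 0.865, which is the reference point below.

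**Why a main effect cannot move the test.** Let g be assignment, s diagnosis and t time.

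- Robustness model: E(y) = a + b·g + c·t + d·g·t + e·s.
- Change from week 0 to time t: c·t + d·g·t. The term e·s has cancelled.
- With complete data the likelihood splits into a part for the changes, which contains c and d but not e, and a part for level given the changes, which has its own intercept, g and s terms. The estimate of d comes from the first part alone.

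REML simulation with 27 per arm agreed. Diagnosis was assumed to shift level by 4 points and change by 2 points per interval.

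| Data | Covariance, time | Mean absolute shift in assignment-by-time from the main effect | SE |
|---|---|---|---|
| Complete | compound symmetric or unstructured, linear or categorical | 0.0000 | 0.76 to 0.81 linear; 1.55 to 1.66 categorical |
| About 15% dropout | compound symmetric, linear | 0.052 | 0.807 |
| About 15% dropout | unstructured, linear | 0.051 | 0.887 |
| About 15% dropout | compound symmetric, categorical | 0.093 | 1.611 |
| About 15% dropout | unstructured, categorical | 0.092 | 1.748 |

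The shifts under dropout are 5% to 6% of one SE (0.092/1.748 = 5.2%; 0.052/0.807 = 6.4%). The SE itself changed by 0.3% to 0.7% on average and by about 2% at most. A separate check with known covariance and 15% missing at week 21 gave a shift with SD about 0.015 points against an SE of about 1.64, or 0.9%. Adding factor-by-time in the near-balanced REML runs gave an SE of 0.94 to 0.97 of the primary-model SE.

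**What omission costs the primary model.** The protocol gives no figure for how far the diagnosis groups differ in change, so b, in within-stratum SDs of change, is varied. Assume equal strata, 27 per arm and no dropout. Leaving the factor out raises the variance of change from 1 to 1 + b²/4, so the SE is multiplied by r = √(1 + b²/4). The 5% critical value is t(52) = 2.007. Then:

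- type I error ≈ 2·P(t52 > 2.007·r)
- power ≈ P(noncentral t52 > 2.007·r), noncentrality 0.85 × √13.5 = 3.123

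| b | r | Type I, formula | Type I, simulated | Power, formula (exact balance) | Power, simulated |
|---|---|---|---|---|---|
| 0 | 1.000 | 0.050 | 0.050 | 0.865 | 0.865 |
| 0.5 | 1.031 | 0.044 | 0.043 | 0.852 | 0.829 |
| 0.85 | 1.087 | 0.034 | 0.034 | 0.824 | 0.797 |
| 1.2 | 1.166 | 0.023 | 0.023 | 0.781 | 0.729 |

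Simulation used 20,000 replicates per cell. With the factor included, type I error was 0.048 to 0.050 and power 0.859 to 0.867 throughout.

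The two power columns differ because 27 is odd. The simulated arms split 13/14 and 14/13, with the extra patient placed against the treatment, which biases the unadjusted effect by b/27 (0.019, 0.031, 0.044). Using (0.85 − b/27) × √13.5 as the noncentrality gives 0.836, 0.794 and 0.731, close to the simulated values. With the extra patient on the favourable side, the same formula gives 0.867, 0.852 and 0.825. The exact-balance column is the fair central figure, and the simulated column is the unfavourable side.

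**The case against.** **The meaning of the covariate term.** In a growth model a patient-level covariate can act on the intercept, the slope or both, and a separate analysis plan might spell this out. That is fair. A main effect is only the plain reading of adding a covariate to an otherwise identical model. If a slope term is meant, the sensitivity analysis is sound once the wording says so. The primary model, whose fixed effects are listed, would still omit the factor.

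**Whether diagnosis predicts change at all.** A reader might infer that the primary confidence interval is certainly too wide. The protocol does not support that. Everyone must score at least 8 on GRID-HAMD, the scale was chosen partly because it covers anxiety symptoms, and the disorders are described as often comorbid. The treatment effects quoted for depression (0.82 to 0.85) and for generalised anxiety, panic and social anxiety (0.82, 0.91, 0.93) are close, although these are between-group effects and only indirect evidence on change. The loss is therefore conditional.

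**Three further readings go too far.**

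- That the check will agree whatever the data show: this is exact only with complete data. Per-protocol and multiple-imputation analyses are also planned, and this point does not touch them.
- That adding factor-by-time would move the estimate substantially: with arms balanced on diagnosis, the shift has an SD of about 0.11 to 0.16 points against an SE of about 1.64. Shifts of 0.24 to 0.55 points arose only with unbalanced allocation, which minimisation is there to prevent.
- That separate effects by diagnosis are required because the Discussion says "This trial has importance especially with regard to the question of the efficacy of UP for depressive disorders": the stated primary hypothesis is pooled, and that sentence sets no subgroup objective.

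**Conclusion.** The point holds in a limited form. On the plain reading, the planned diagnosis check is uninformative: it has no effect on the tested contrast with complete data and moves it by about 6% of an SE or less, on average, at the planned dropout.

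The omission from the primary model is an efficiency matter. Its direction is conservative: it does not create false positives. Across assumed diagnosis differences in change of 0 to 1.2 SD, type I error runs from 0.050 down to 0.023. Power runs from 0.87 down to 0.78 with exact balance, or to 0.73 with one patient's imbalance against the treatment, compared with about 0.86 when the factor is included. At zero difference nothing is lost.

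These figures assume 27 evaluable patients per arm, equal strata, and an SMD of 0.85 measured against the within-stratum SD. The protocol does not say which SD its 0.85 refers to. If it is the overall SD, the same gap would appear mainly as power gained by including the factor. The stated sample size is not affected.

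**What to change.** Put the minimisation factor and its interaction with time in the primary model, for GRID-HAMD and for the continuous secondary outcomes, and make the model without the factor the sensitivity analysis. State the terms explicitly, so that the word covariate is not left to interpretation, and fix the wording before unblinding.

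The cost is one main-effect parameter plus one interaction parameter if time is linear, or two if it is categorical. No new data are needed, and the simulations show essentially no loss of power when diagnosis is unrelated to change. Estimates within each diagnostic group may be reported descriptively, but they are optional and would be imprecise with 54 patients.
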